### 3.3 Exclusion Criteria

8. Currently pregnant, planning to become pregnant during the study period, and/or breast feeding
9. Known hypersensitivity/allergy to hydroxychloroquine or to 4-aminoquinoline compounds.
10. Current use of hydroxychloroquine for the treatment of a medical condition.
11. Known prolonged QT syndrome and/or baseline resting ECG with QTc > 450 ms (completed in the last 3 months) and/or concomitant medications which simultaneously may prolong the QTC that cannot be temporarily suspended/replaced. These are including but not limited to Class IA, IC and III antiarrhythmics; certain antidepressants, antipsychotics, and anti-infectives; domperidone; 5-hydroxytryptamine (5-HT)3 receptor antagonists; kinase inhibitors; histone deacetylase inhibitors beta-2 adrenoceptor agonists.
12. Known pre-existing retinopathy, G6PD deficiency, porphyria, liver disease including cirrhosis, encephalopathy, hepatitis or alcoholism, diabetes on oral hypoglycemics or insulin, or renal insufficiency/failure.
13. Disclosure of self-administered use of hydroxychloroquine or chloroquine within 12 weeks prior to study. This window allows five half-lives of HCQ (i.e. 21 days) to pass before being reintroduced to the drug.
14. Confirmed symptomatic COVID-19 at time of enrollment, i.e. symptom of COVID-19 at enrollment with confirmation of SARS-CoV-2 infection by viral detection as performed according to local guidelines for symptomatic HCWs. All participants with COVID-19 symptoms at enrollment will be directed to have confirmatory testing (within the department or occupational health as per the site guidelines). Participants who are negative for SARS-CoV-2 will be redirected to enrollment procedures; those testing positive will be excluded.

Site investigators are required to assess any concomitant medications being taken at the time of study enrollment to ensure they are not exclusionary based on criterion #3 above. In cases of uncertainty, the investigator is encouraged to consult with the study pharmacist (see contact information in section Study Contact Details, page 6).

### 3.4 Strategies for Recruitment

Eligible staff will be invited *via* email to an online information forum in which study information and eligibility will be discussed in general. In addition to this email, a poster outlining a brief overview of the study and contact information will be displayed in the hospital sites in areas and departments where relevant cadres of HCW will view the poster. This is congruent with currently recommended physical distancing practices. Staff willing to participate and who feel that they meet eligibility criteria will be able to schedule an individual appointment with study coordinators over subsequent days which will provide them with the opportunity to ask questions about participation, confirm eligibility, sign a written consent form, and complete an enrollment visit/procedures.

### 3.5 Enrollment Procedures

Study staff will complete enrollment procedures with participants in a private room. Enrollment will be scheduled on a first come, first served basis over the pre-specified scheduled days. Any participant screening positive for symptoms of COVID-19 (see Symptom Screen in Questionnaire Content/Appendix B) will be directed to the most appropriate place for a confirmatory COVID-19 test (within the emergency department or occupational health as per site institutional guidelines). Of these, participants who have a negative COVID-19 screen will be redirected to enrollment procedures, persons with a positive COVID-19 screen will be excluded.

The consent process will involve obtaining a signed copy of the REB-approved written informed consent form. Participants will be interviewed by study staff, asked to submit a baseline socio-demographic questionnaire, have a venous blood sample drawn, and provide a self-collected viral detection specimen.

### 3.6 Co-enrollment Guidelines

Co-enrollment into other investigational prevention studies will not be permitted at this time.

## 4.0 WITHDRAWAL OF PARTICIPANTS

### 4.1 Withdrawal criteria

Participants may be withdrawn from the study if the Sponsor-Investigator terminates the trial (i.e. if new evidence emerges proving either futility or efficacy of the study drug or

potential safety concerns or if drug supply becomes an issue). Grade 3 or 4 adverse events or an SAE may warrant withdrawal from the study. If a new health condition emerges in a participant randomized to the HCQ arm that requires medications absolutely contraindicated by the protocol, then decisions regarding discontinuation of the study drug can be made at the discretion of the site investigator, but the participant should be retained in the study for ascertainment of the primary and secondary outcomes. Site investigators are encouraged to consult with the study pharmacist in such situations. Reasons for the discontinuation of study drug will be noted in the study database. If the participant discloses that they have been self-administering any other medication for the prevention of COVID-19, it will be noted in the database and the participant will be retained in the study for ascertainment of primary and secondary outcomes. If a participant withdraws from the medication, with consent, the participant will still be followed for primary and secondary outcomes.

## 5.0 RANDOMIZATION AND BLINDING PROCEDURES

### 5.1 Randomization

Once a participant signs the informed consent document, the Research Coordinator will issue a Study ID number and enter the Study ID into a secure web-based randomization system that will be housed at the Applied Health Research Centre (AHRC) at St. Michael's Hospital. Randomization will occur through this central system which provides adequate allocation concealment to perform randomization. Randomization will be in a 1:1 ratio with permuted blocks of variable size and stratified by study site. The randomization sequences will be pre-determined by a non-trial statistician who will be the only person with access to the study codes. An automated audit trail will record the time, date, allocation, and participant identification numbers.

### 5.2 Blinding

This trial is fully-blinded, at the level of the participant, study coordinator, and investigator. Study drug and placebo will be identical in appearance and will be provided by the manufacturer. They will be packaged in identical bottles and dispensed by the Research Clinical Trials Pharmacy at UHN.

Blind will only be broken if an immediate safety issue arises for a participant in which knowledge of the treatment allocation will impact clinical care. The Medical Monitor of the study must be consulted in these situations.

When interim analyses are conducted, the study coordinator will send relevant data from participants enrolled and the codes to be included in the interim analysis to the biostatistician working with the Data Safety and Monitoring Board.

## 6.0 STUDY TREATMENTS

### 6.1 Investigational Product

#### 6.1.1 Description

Brand or Product Name: Apo-Hydroxyquine

Manufacturer: Apotex

Generic Name: Hydroxychloroquine

DIN - 02246691

Hydroxychloroquine (HCQ) sulfate tablets belong to the 4-aminoquinoline class. HCQ has been beneficial for patients with rheumatoid arthritis and lupus erythematosus, especially chronic discoid lupus. The exact mode of action in controlling these diseases is unknown. The action of this compound against malarial parasites is similar to that of chloroquine phosphate: interferes with glycosylation of cellular ACE2 receptor (COVID-19 uses ACE2 receptors to bind to target cells), impairs acidification of endosomes which is required for virus/cell fusion, along with other immunomodulatory effects.

#### 6.1.2 Expected Side Effects:

Most side effects are seen in treatment doses and in long term use (over years). Most are reversible with stopping the medication (unless otherwise indicated):

**Very Common: (>10%):** Abdominal pain, nausea

**Common: (1-10%):** Blurring of vision due to a disturbance of accommodation, diarrhea, vomiting, anorexia, headache, affect lability, skin rash/pruritis,

**Uncommon: <1%:** Vertigo, tinnitus, maculopathies (in early form is reversible), abnormal liver function tests, dizziness, nervousness, pigmentary changes in skin, hair

**Not known (event rate):** blood disorders, cardiomyopathy, prolonged QTC, urticaria, angioedema, bronchospasm, myopathy

**Serious:** Most serious toxicities are associated with long term use (ie. over years) and include: retinopathy, liver dysfunction, and hemolysis in G6PD deficient patients (NB: Product monograph suggests G6PD testing prior to initiation but post-marketing studies suggest risk is low and in standard clinical practice this is not done.)

## 6.2 Formulation and packaging

The manufacturer Apotex will provide study medication (hydroxychloroquine and matching placebo). The pharmacy department of the University Health Network will be responsible for labelling and distribution of study medication. Study medication will be stored by the pharmacy in accordance with relevant guidelines. The study medication is supplied in tablet formulation and dispensed in bottles labelled in the following way: dispensing label (including patient name, directions for use, prescriber) and the Health Canada label (to meet standards for investigational drug).

## 6.3 Placebo

Matched placebo will be provided from the manufacturer Apotex.

### 6.3.1 Expected Side Effects

There are no expected side effects from the placebo.

### 6.3.2 Formulation and packaging

Placebo will be provided in the same format as described above for the interventional drug.

## 6.4 Study Product Supply and Accountability

All study medications will be stored at 15-30°C in a secure location. Study medication will be collected from the pharmacy department by the principal investigator or his/her delegate. Unused or partially used investigational products (IP) will be returned to the study coordinator. Destruction of the IP via Stericycle will be coordinated with the site pharmacy of each participating institution

The study medication should be stored in a secure area according to local regulations. The investigator is responsible for ensuring that it is dispensed only to study subjects and only from official study sites by authorized personnel, as dictated by local regulations.

The investigator is responsible for ensuring that the study medication is stored under the appropriate environmental conditions (temperature). If concerns regarding the quality or

appearance of the study medication arise the study product will not be dispensed and Apotex will be contacted immediately.

## 6.5 Dosing and Administration

During the randomization period (90 days), HCQ will be administered as 400mg orally once daily in the treatment arm and placebo tablets will be administered similarly once daily for 90 days. The open-label extension period will offer all participants HCQ 400 mg orally once daily for one month.

## 6.6 Concomitant Medications

Study investigators must review concomitant medications at enrollment as part of eligibility criteria for enrollment. Investigators are encouraged to consult with the study pharmacist in cases of uncertainty. All other concomitant medications will be collected at study visits and recorded.

## 6.7 Dispensing Investigational Product to participants

### 6.7.1 Initial Visit

Once a participant signs the informed consent document, the Research Coordinator will issue a Study ID number and enter the Study ID into a secure web-based randomization system (REDCap) that will be housed at the Applied Health Research Centre (AHRC) at St. Michael's Hospital. Randomization will occur through this central system which provides adequate allocation concealment to perform randomization. Randomization will be in a 1:1 ratio with permuted blocks of variable size and stratified by study site. The randomization sequences will be pre-determined by a non-trial statistician. The randomization code will be a 6 digit number not related to the participant's study ID number. An automated audit trail will record the time, date, allocation, and participant identification numbers.

Once the study coordinator has the participant's randomization code, this will be communicated to the clinical trials pharmacy by email. The clinical trials pharmacist will dispense the appropriate investigational product (IP) by cross referencing the randomization code of the participant to the randomization list provided by the trial statistician. The study coordinator will pick up the IP bottles from the clinical trials pharmacy at an agreed upon time and deliver it to the study participant.

### 6.7.2 Subsequent Study Visit

For subsequent study visits, the study coordinator will email the clinical trials pharmacy 24 hours prior to the scheduled visits to request the IP bottles required. The clinical trials pharmacy will dispense the requested IP bottles to the study coordinator who will dispense them to the participant at the study visit.

### 6.7.3 Dispensing through non-UHN sites

For additional trial sites, the central pharmacy at UHN will prepare the IP according to the randomization codes and ship to the pharmacies of other sites via courier. Local Standard Operating Procedures for accountability will be verified and approved prior to issuing and dispensing IP through these sites.

## 6.8 Participant Access to Study Medication at Study Closure

At the end of the 90-day randomization period, all participants will be offered a 30-day open-label extension of hydroxychloroquine 400 mg orally daily. Beyond the study period, HCQ is not currently indicated for routine prophylaxis of viral infections. If the study is terminated for efficacy, all participants will be offered the 30-day open-label extension at that time.

In the event that a study participant tests positive for COVID-19, participants will be instructed to stop their study drug. If this occurs during the randomization period, neither participant nor study staff will not be unblinded to allocation group. Efforts will be made to link the individual to ongoing clinical trials of COVID-19 treatment if such trials are enrolling in proximity to the study site and the participant meets the inclusion criteria. However, no guarantees of access to investigational product can be made. At the time of writing, there are no known effective treatments for established COVID-19 infection.

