## 8.0 CLINICAL AND LABORATORY EVALUATIONS

### 8.1 Clinical Evaluations

All in-person study visits will begin with a COVID-19 symptom screen (see Questionnaire Content document). If the participant fails the symptom screen, a surgical mask should be placed on the participant and full droplet/contact precautions will be followed by study staff (i.e. surgical mask, eye protection, gown, glove). Any participant screening positive for symptoms of COVID-19 will then be directed to the most appropriate place for a confirmatory COVID-19 test (within the department or occupational health as per site institutional guidelines).

For all COVID-19 screen negative participants, study staff will conduct brief interviews to document medical history (baseline comorbidities and medications at day 1 and then new comorbidities, medications, adverse events and side effects at day 30,60,90,120). No physical examinations are required in this study. All WOCs will have a screening urine test at Day 1, 30, 60 and 90. All participants will have a review of a baseline QTc interval measure at Day 1 and a repeat QTc measure at Day 30, 60, 90 and 120. Participants

with a baseline QTc between 430-450 ms will be referred for a repeat QTc measure within 72 hours of commencing study drug.

All side effects will be documented by the study coordinator. The study coordinator has experience in implementing clinical trials of investigational agents and collecting and documenting AEs/SAEs. It is the study physician who will assess severity and relationship to study drug. If the side effect is attributed to the study tablet and has an impact on the participant's functional status (ex. ability to work) or general state of well being, the Study Physician will be responsible for further follow up. Ultimately, the participant will be supported in any decision they make regarding the continuation of study tablets.

If a participant becomes COVID-19 positive at any time in the study, all further in-person clinical evaluations will occur remotely (via telephone call) in light of necessary self-isolation and reducing risk to study staff. They will not have further respiratory specimens or phlebotomy collected while they have symptomatic COVID-19.

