#### 9.4 Study Visits 1-4 (Follow-up at Day 30, 60, 90, and 120): Conducted in person.

Participants will be schedule for monthly Study Visit appointments. These are expected to take a maximum of 30 minutes, and in many cases much less. Whenever possible, the study visits will be coordinated with the participant's scheduled ED shift in order to minimize travel and burden on the participant. The components of the Study Visit are as follows:

- **Interview:** The coordinator will review the participant's COVID-19 symptom reporting, their responses to the Adverse Events Questionnaire and Tolerability Questionnaire. The research coordinator will review the responses prior to releasing the next installment of study drug/placebo. If the participant has any concern regarding adverse events or other aspect of the study, they will have the opportunity to discuss these with the research coordinator during the visit.
- **Urine pregnancy test:** for women of childbearing potential.
- **Self-collected viral detection sample:** As above.
- **Blood for serology and other laboratory markers:** As above.
- **QTc interval evaluation:** The QTc will be measured and recorded.
- **Dispense study drug:** The coordinator must confirm receipt of the package with the participant, and review dosing.
- **Psychological distress questionnaire:** will be emailed to participant to complete at day 60 and day 120.

Participants with confirmed COVID-19 will be asked to discontinue their study tablets (see Section 6.7). They will not present for in person visits until they are cleared to return to work.

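### The entry limits on QTc, medication and medical conditions are not linked to the open-label HCQ offer, at which the placebo arm first takes the drug

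*Protocol*

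**What the plan says.** **Entry.** Section 3.3 (and the synopsis) excludes "Known prolonged QT syndrome and/or baseline resting ECG with QTc > 450 ms". It also excludes people on QT-prolonging medication that cannot be suspended or replaced, and people with listed conditions. On medication it adds: "Site investigators are required to assess any concomitant medications being taken at the time of study enrollment". Section 6.6 likewise places the eligibility review of medication at enrollment.

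**Start of blinded drug.** Under Section 8.1, participants "with a baseline QTc between 430-450 ms will be referred for a repeat QTc measure within 72 hours of commencing study drug".

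**Open-label HCQ.** Sections 6.5 and 6.8 offer it to everyone: "At the end of the 90-day randomization period, all participants will be offered a 30-day open-label extension of hydroxychloroquine 400 mg orally daily". There are two further routes. Section 6.8 makes the offer immediately if the trial stops for efficacy. The special schedule considerations under Section 9.1 let a participant who has recovered from COVID-19 and been cleared for work go straight to the open-label month.

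**What happens at Day 90.** Section 8.1, Section 9.4 and Table 1 schedule a QTc, a urine pregnancy test for women of childbearing potential, and an interview covering "new comorbidities, medications, adverse events and side effects at day 30,60,90,120". Section 6.6 says of medication after entry: "All other concomitant medications will be collected at study visits and recorded". Section 9.4 has the coordinator go through COVID-19 symptom reporting and the adverse-event and tolerability questionnaires: "The research coordinator will review the responses prior to releasing the next installment of study drug/placebo". For QTc, Section 9.4 provides only for measuring and recording it.

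**Other rules after entry.** Section 4.1 leaves it to the site investigator whether to stop study drug when a new condition requires a contraindicated medication, but it is worded for participants allocated to HCQ. Section 7.1 has study drug stopped in pregnancy. Section 10.1 stops study medication for toxicity.

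**The concern.** The exclusions protect participants against HCQ, yet they are worded for the day a participant enters the trial. For the placebo arm, that is not the day HCQ starts. Under the text as written, a placebo participant who has crossed one of the protocol's own limits by Day 90, for example through a QTc above the entry limit or a newly prescribed QT-prolonging drug, is still offered HCQ.

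The borderline-QTc check has the same problem. The protocol judged that a baseline of 430-450 ms calls for an early repeat after study drug begins. Section 1.3 says that HCQ can lengthen the QT interval and that the frequency can rise with other QT-prolonging drugs. In the placebo arm that early repeat is taken on placebo, and no counterpart is scheduled when HCQ begins. The stake is participant safety in the extension; the primary efficacy comparison is not in question here.

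**Working it through.** No sample-size, power or error-rate figure bears on this point. The check is a comparison of provisions with two small calculations.

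**1. Who first takes HCQ in the extension.** Inputs: 988 participants (Section 3.1) and 1:1 allocation (Section 5.1). 988 / 2 = 494 on placebo. This is an upper figure, because it assumes that all of them reach the extension and accept the offer.

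**2. Does any provision connect the limits to that first HCQ dose?**

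| Provision | What it does | Does it reach a placebo participant about to start HCQ? |
|---|---|---|
| 3.3, synopsis | QTc, medication and condition limits | Worded for baseline or enrollment |
| 6.6 | Medication checked for eligibility at enrollment, recorded afterwards | Recorded, no action attached |
| 8.1, Table 1 | QTc and interview at Day 90 | Data collected, no threshold or action attached |
| 9.4 | Symptom, adverse-event and tolerability responses reviewed before release | Entry limits not named |
| 4.1 | Discretion over newly needed contraindicated medication | No, worded for the HCQ arm |
| 7.1 | Drug stopped in pregnancy | Yes, for pregnancy |
| 10.1 | Drug stopped for toxicity | Not before HCQ has been taken |

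Only pregnancy carries a stated consequence that would reach this group before the first HCQ dose. Section 4.1 has a second difficulty: Section 5.2 blinds participant, coordinator and investigator, so a rule that depends on being in the HCQ arm cannot be applied as worded during the randomized period.

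**3. The borderline check.** In the placebo arm, starting study drug means starting placebo, so the 72-hour repeat shows nothing about HCQ. After Day 90 the next scheduled QTc is at Day 120. Both visits have a window of ±7 days (Table 1):

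- nominal interval: 120 − 90 = 30 days
- shortest: (120 − 7) − (90 + 7) = 113 − 97 = 16 days
- longest: (120 + 7) − (90 − 7) = 127 − 83 = 44 days

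These are intervals between measurements. They compare with 72 hours for the same band when blinded drug starts.

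**4. How many are in the band.** The protocol does not give the share with a baseline QTc of 430-450 ms, so the number cannot be derived. Purely as an assumption, 5% to 20% of 494 would be 494 × 0.05 ≈ 25 to 494 × 0.20 ≈ 99 placebo participants.

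**5. Starts outside Day 90.** The table in Section 11.3.3 places the interim analysis at month 1.7, and an efficacy stop would trigger the offer then. A recovered participant may start after a spell of telephone visits (Sections 8.1 and 9.1). Neither route states a link to the entry limits or to a QTc measurement.

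**The case against.** The strongest reply is that Day 90 is already well covered. QTc is measured, new medications and comorbidities are asked about, pregnancy is tested, and Section 9.4 lists QTc and the pregnancy test ahead of dispensing. Section 7.3 adds monthly in-person safety follow-up and an independent monitoring board. An investigator who saw an abnormal QTc would probably act on it, and the operations manual, which is not at hand, may say so. All of this is fair. A reader might infer that placebo participants start HCQ with no checks at all, and that reading is wrong. What is missing is a criterion that connects the results to release of the drug.

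Three other inferences also fail:

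- **That the entry ECG is out of date when HCQ starts.** QTc is repeated at Days 30, 60 and 90, so a placebo participant reaches the Day 90 offer with a current measurement. At Day 1, by contrast, the protocol accepts an ECG up to three months old.
- **That the exclusions and the Day 90 offer contradict each other.** An entry criterion and a later offer can both hold. The protocol leaves the relation between them unstated, which is a gap to be reconciled.
- **That the whole placebo arm is monitored less closely than the HCQ arm was.** Outside the 430-450 ms band, the HCQ arm's first scheduled QTc on drug is Day 30, the same nominal 30 days as Day 90 to Day 120. The scheduled difference is confined to the borderline group.

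The toxicity rule in Section 10.1 and the discretion in Section 4.1 do not close the gap. The first concerns harm after exposure, and the second excludes this group by its wording.

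**Conclusion.** The point holds as an unreconciled gap. The QTc, medication and condition limits apply by their wording at entry. The Day 90 data that could be compared with them are collected but carry no consequence for the open-label offer. The only later rule on contraindicated medication leaves out placebo participants about to start HCQ. The borderline-QTc check falls on placebo for the placebo arm, with 30 days nominally (16 to 44 with the windows) between the Day 90 and Day 120 measurements.

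Up to about 494 participants would first take HCQ in the extension. That figure counts first exposure under full uptake, and a reader should not take it as a number harmed or even a number over a limit. The protocol gives neither the share in the borderline band nor the share crossing a limit by Day 90, so the number affected is unknown. The conclusion rests on the protocol text alone; procedures held in the operations manual could narrow it in practice.

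**What to change.** Reconcile Sections 3.3, 4.1, 6.6, 6.8, 8.1, 9.1 (special schedule considerations) and 9.4:

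1. State in Section 6.8 whether the protocol's own QTc, medication and condition exclusions govern release of open-label HCQ, separately for the Day 90 route, an efficacy stop, and recovery from COVID-19.
2. If they do, state that the QTc, interview and pregnancy data already collected at Day 90 are reviewed against them before release. For the other two routes, state which data are used.
3. Extend or reword the Section 4.1 rule so that it is not limited to the HCQ arm.
4. State in Section 8.1 whether the 430-450 ms referral attaches to the first open-label dose.

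The clinical limits are for the sponsor to set.

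**Cost.** A short amendment. Linking the existing Day 90 data to release needs no new procedure. The early routes may need a measurement that is not otherwise scheduled at that moment, and so would a repeat QTc if the referral is attached to open-label HCQ. If the exclusions are applied, a few participants may not receive the open-label month they were promised. Section 2.1 relies on that promise to support adherence, so participants would need to be told.
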